One new FBAO intervention that has been described in the past decade is airway clearance devices (ACDs). These externally applied, non-powered, portable suction devices have been marketed as an alternative when traditional FBAO techniques fail and fall into two broad types, which, despite their similarities, have considerable differences in their design. Non-invasive ACDs are primarily manufactured by LifeVac© (LifeVac LLC, Nesconset, New York, USA), and consist of a facemask attached to a compressible bellows system [10]. Applying the mask to the choking person’s face creates a seal, followed by a rapid depression of the plunger system and a firm pull upwards. Minimally invasive ACDs are primarily manufactured by Dechoker© (Dechoker LLC, Concord, NC, USA), and consist of a short oropharyngeal tube that acts as a tongue depressor when the external face mask is applied [11]. The attached cylinder has a plunger that is pulled sharply to create the negative pressure system once a seal is formed with the mouth. Both contrast with other suction devices (e.g., Laerdal© V-Vac®) that do not have the external anchor of the face mask and can enter deeper into the oral airway [12]. Both devices offer training primarily through online videos from their websites, which can be viewed by purchasers and the public. 

However, two independent systematic reviews recently conducted concluded that there is insufficient evidence to support or discourage ACD use in the treatment of FBAO [6,13]. Both reviews only identified ten unique cases describing the safety of LifeVac’s ACD, all of which were successful at FBAO relief with no adverse events documented. They concluded with a recommendation that further evaluation in a research setting would be beneficial to determine the safety and effectiveness profile of ACDs.

Updated evidence in this area is required urgently. As sales of ACDs are increasing worldwide, the public and resuscitation councils require them to make informed decisions on their utility [10,11]. If the safety and effectiveness profile remain promising, then acknowledging ACDs as an alternative to traditional techniques is appropriate. If not, then this also needs to be clarified. Regardless, the first step in this process is to conduct research, independent of industry, examining these outcomes further.

This protocol details the present study’s proposed method to address the following objectives:

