Research Aim One: To investigate what situational and patient factors are frequently identified, and which are associated with relief of the FBAO and survival in individuals with a FBAO treated with an ACD.

Research Aim Two: To describe the experiences of individuals who have used ACDs in response to a FBAO and identify facilitators and barriers to the use of ACDs compared to traditional interventions.

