## Results

Study one: analysis of the prospective database 

Descriptive statistics will be used to summarize the demographic, situational, outcome, and adverse event data. This will include proportions, means (standard deviations), and medians (interquartile ranges) with associated 95% confidence intervals as appropriate for the variable type. 

Relief of FBAO will be defined as the resolution of choking symptoms with no further intervention (by bystanders or EMS) required. It will be a binary variable coded as "success" or "failure." Survival will be coded as alive or dead. Survival with a favorable neurological outcome will be assessed using the cerebral performance category (CPC), with a favorable outcome being a category of 1 or 2 (good or moderate) [15]. A CPC will be assigned by the researchers after reviewing participant answers about post-FBAO functional abilities. Adverse events (both patient-related and device-related) will be summarized using descriptive statistics.

One of the medical researchers (SO, KV, or CD) will assess the information for each case to ensure appropriate assignment of outcomes. All of these will be second checked by one of the physician investigators (DS or CD) to ensure accuracy and reliability. The bivariable analysis will be performed using either the student’s T (continuous) or Chi-squared test (categorical, Fisher’s exact test if n <5) to measure the association of collected data with these outcomes. In all cases, statistical significance will be defined at the level of p <0.05 for comparative analysis. 

The stratified analysis will look at clinically important subgroups including adult versus pediatric patients, mild versus severe FBAO, patients with neurological and neurocognitive impairment, type of ACD used (e.g., non-invasive versus minimally invasive), and users’ prior training (e.g., first responder/healthcare worker versus first aid trained versus layperson without training). Finally, outcomes will also be stratified by whether individuals received a single FBAO intervention (e.g., only ACDs) or multiple (e.g., back blows followed by ACDs). This is important to note because any resolution of symptoms after multiple interventions is likely due to a synergistic effect as opposed to one intervention being solely responsible.

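### Association with relief and survival is decided by p<0.05 alone, with no effect estimate and interval for the contrast; if failures or deaths are few, that criterion may be unattainable

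*Protocol article*

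**What the plan says.** Aim One (protocol article, end of the Introduction) asks which situational and patient factors are frequent and "which are associated with relief of the FBAO and survival in individuals with a FBAO treated with an ACD".

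The method is in Results, under the analysis of the prospective database. Relief is binary (success or failure), and for survival "Survival will be coded as alive or dead". Factors are compared by Student's t for continuous data, or by "Chi-squared test (categorical, Fisher’s exact test if n <5) to measure the association of collected data with these outcomes". The criterion follows: "In all cases, statistical significance will be defined at the level of p <0.05 for comparative analysis".

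Intervals appear earlier in the same section, for the descriptive summaries: "This will include proportions, means (standard deviations), and medians (interquartile ranges) with associated 95% confidence intervals as appropriate for the variable type". The section also plans outcomes by subgroup (age group, severity, impairment, device type, training, single or multiple interventions) and promises the n for each analysis.

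No expected number of reports, failures or deaths is given. On prior device cases, the Introduction cites ten, "all of which were successful at FBAO relief with no adverse events documented"; Table 2 in the Discussion lists one case series of 10 patients for each of relief and survival.

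**The concern.** The tests are said to serve "to measure the association of collected data with these outcomes", but a t, chi-squared or Fisher p-value does not measure association. It mixes the size of the association with the number of events and the balance of the groups. With a binary outcome, the rarer category limits the information. If only a handful of failures or deaths are reported, a factor may fail the 0.05 criterion because of that count alone, however strongly it is related to the outcome.

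Aim One is at stake, because it asks which factors matter. Under the stated criterion a strong factor could go unnamed, and the reader would have no estimate or interval of the contrast to show that the data were merely uninformative. If deaths are fewer than failures, survival is the more exposed outcome. The Discussion expects the results to help shape guidelines, so the reading of non-significant factors has consequences.

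**Working it through.** The article gives no power, sample size or effect size, so there is no planned figure to reproduce. From the article: alpha 0.05, the named tests, binary outcomes and 10 of 10 prior successes. Assumed here: two-sided tests, total N from 50 to 400, and the failure rates shown below.

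**1. Can the criterion be met?** For a factor that splits N reports evenly, the most extreme table puts all k failures on one side. The smallest two-sided Fisher p is

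p_min = 2 × C(N/2, k) / C(N, k).

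For N=100 and k=5: 2 × 2,118,760 / 75,287,520 = 0.056.

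| N | k=4 | k=5 | k=6 |
|---|---|---|---|
| 50 | 0.110 | 0.0502 | 0.022 |
| 100 | 0.117 | 0.056 | 0.027 |
| 150 | 0.120 | 0.058 | 0.028 |
| 200 | 0.121 | 0.059 | 0.029 |
| 400 | 0.123 | 0.061 | 0.030 |

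With 5 or fewer failures and N of 50 or more, an evenly split factor cannot pass. More successful reports do not help, because p_min rises with N.

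**2. Uneven factors.** For a factor present in 20 of 100 reports, 2 failures suffice if both fall in the small group: C(20,2)/C(100,2) = 190/4,950 = 0.038. If all failures fall in the large group, 14 give p=0.066 and 15 give p=0.037. One threshold therefore treats factors, and directions, unequally.

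**3. How likely are 5 or fewer failures?** Binomial probability under assumed failure rates:

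| N | Failure rate | P(at most 5) |
|---|---|---|
| 50 | 5% | 0.96 |
| 50 | 10% | 0.62 |
| 100 | 2% | 0.98 |
| 100 | 5% | 0.62 |
| 100 | 10% | 0.06 |
| 200 | 5% | 0.06 |
| 150 | 10% | 0.002 |

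The prior data do not settle the rate. With 0 failures in 10, the exact 95% upper limit is 1 − 0.025^(1/10) = 30.8%.

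**4. Power when the criterion is attainable.** All 2×2 tables were enumerated for an evenly split factor, using Fisher's test if any observed cell is below 5 and uncorrected chi-squared otherwise:

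| Failure rates | N=100 | N=200 |
|---|---|---|
| 2% v 6% | 3% | 17% |
| 5% v 15% | 25% | 66% |
| 10% v 30% | 70% | 96% |

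Expected failures at N=100 are 4, 10 and 20.

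**5. What an effect estimate adds.** Hold the risk ratio at 3.0 with 100 reports per group, and take the Wald interval on the log scale, SE = √(1/a − 1/100 + 1/b − 1/100):

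| Failures a v b | 95% CI for the risk ratio | Fisher p |
|---|---|---|
| 3 v 1 | 0.32 to 28.4 | 0.62 |
| 6 v 2 | 0.62 to 14.5 | 0.28 |
| 9 v 3 | 0.84 to 10.8 | 0.13 |
| 12 v 4 | 1.00 to 9.0 | 0.065 |
| 15 v 5 | 1.13 to 7.9 | 0.032 |

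The estimate stays at 3.0 and the interval shows the imprecision; the p<0.05 result changes with the failure count alone. At 12 v 4, chi-squared gives 0.037, so the result also turns on whether the trigger for Fisher's test means observed counts (smallest 4) or expected counts (smallest 8), which the article does not say.

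A second example: 5/25 v 0/25 failures is a 20-point difference with a Newcombe 95% interval of 3 to 39 points, while Fisher's p is 0.0502.

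**The case against.** The strongest reply has four parts.

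- **The text attaches no meaning to p≥0.05.** A reader might infer that the plan will list such factors as not associated. The article never says so; it only defines significance. That reading is unsupported and forms no part of this point. What remains is that nothing tells the reader such results are inconclusive.
- **The p-value does not stand alone.** Proportions with 95% intervals, outcomes by subgroup and the n of each analysis are planned, so imprecision would not be wholly hidden. This stands, and it narrows the point to the missing contrast: separate proportions are not an interval for their difference.
- **Few failures is not established.** No N or rate is stated, the Discussion says self-reporting skews toward extremes such as success or death, and an independent website is meant to encourage unfavourable reports. This stands: the sparse-event problem is conditional. With no failures at all, no method could estimate an association, so that case is no fault of the chosen tests.
- **The article is condensed, and an analysis plan may name the effect measure.** It may. But the article does not leave the method open: it gives the tests the task of measuring association and fixes one criterion for all comparisons. If a fuller plan names a contrast, the article need only carry it over.

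The disclaimer that no percent effectiveness will be claimed limits claims about the devices. It does not address the tests of which factors matter.

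**Conclusion.** The point holds in a limited form. For Aim One, p<0.05 is the only stated criterion for association, and no effect estimate with an interval is named for the contrast. If failures or deaths number 5 or fewer with 50 or more reports, an evenly split factor cannot meet that criterion by Fisher's test. With 4 to 10 expected failures at N=100, power for roughly threefold differences is about 3% to 25%. A non-significant result would then say little about association.

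This rests on two-sided tests and on assumed N and failure rates. With about 40 failures in 200 reports (10% v 30%) power is 96%, and an uneven factor can reach significance with 2 failures in its small group. It would be too strong to say that real associations will generally be missed. The change is worth making because it helps at any event count and costs little.

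**What to change.** In Results, in the analysis of the prospective database, amend the text on bivariable analysis so that, for each factor:

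- events and denominators are shown by factor level for each outcome;
- the association is reported as a risk difference or odds ratio with a 95% interval (Newcombe, exact or penalised where cells are sparse), or as a mean or median difference with an interval for continuous factors;
- the p-value is kept as secondary;
- the text states that p≥0.05 is inconclusive and is not evidence of no association.

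This takes two or three sentences and standard software, and no more participants. The downside is slightly more output and some wide intervals. The intervals will show the imprecision of sparse data, not remove it.

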Data will be collected in four domains: participant (ACD user), patient (choking person), situational, and outcome (Table 1). Furthermore, participants will be asked to make several agreement statements to further assess their experience.

**Table 1 TAB1:** Summary of collected variables via online survey. ACD: airway clearance device; CPR: cardiopulmonary resuscitation; EMS: emergency medical services; FBAO: foreign body airway obstruction.

Data category	Variables
Participant (ACD user)	Demographics, relationship to the person who choked, previous first aid or medical training, and previous experience with airway clearance devices (e.g., training, practice, or personal use)
Patient (choking person)	Demographics, medical comorbidities, functional status pre-FBAO, and FBAO history
Situational	Date and location of FBAO, foreign body details, witnessed status, severity of FBAO, patient status at time of intervention (e.g., consciousness, crying/speaking), FBAO intervention details, ACD intervention details, CPR intervention details, and EMS activation
Outcome	Relief of FBAO, survival, survival with good neurological function, functional status post-FBAO, and adverse events

Participants will be provided with an email contact for the research team in case they are unsure how to respond to a particular question and want clarification before submitting their response. Further, all participants will be asked to consent to receiving a follow-up email in the event the research team requires clarification of their responses to ensure accuracy of responses as well as confirmation that the event occurred. Once their responses are checked by one of the research team members for clarity and follow-up is conducted if needed, the results of the survey questions will be de-identified and assigned a unique study ID.

Study two: qualitative evaluation of ACD users’ experiences

Participants and Recruitment Procedure

Participants in this study will be a subset of the individuals who participated in study one (prospective evaluation). All participants after January 1st, 2022, will be invited to consent to an optional interview further discussing their experiences with ACDs. A six-month delay will occur to ensure the research design for the prospective study is functioning effectively before integrating the optional interviews.

Data Collection

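### The single-versus-multiple stratification is not anchored to the first ACD attempt, so relief in the ACD-only group is biased upward whenever failed ACD-first cases go on to another technique

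*Protocol article*

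**What the plan says.** All of the rules are in the Protocol article.

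- **Outcome** (Results, Study one): "Relief of FBAO will be defined as the resolution of choking symptoms with no further intervention (by bystanders or EMS) required". It is coded as a binary variable.
- **Stratifier** (same section): "outcomes will also be stratified by whether individuals received a single FBAO intervention (e.g., only ACDs) or multiple (e.g., back blows followed by ACDs"). The reason given is that "any resolution of symptoms after multiple interventions is likely due to a synergistic effect as opposed to one intervention being solely responsible".
- **Association tests** (same section): t, chi-squared or Fisher's exact tests are used "to measure the association of collected data with these outcomes", and "statistical significance will be defined at the level of p <0.05 for comparative analysis".
- **Data collected** (Materials and methods, Table 1): the situational variables include "FBAO intervention details, ACD intervention details, CPR intervention details, and EMS activation".
- **Aim One** (Introduction): "To investigate what situational and patient factors are frequently identified, and which are associated with relief of the FBAO and survival".

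The stratifier carries no time point relative to the ACD. The relief definition does not say what an intervention must be further to: the ACD attempt, or the last technique tried.

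**The concern.** A stratum should be fixed before the outcome it is used to describe. As worded, this one need not be. Of two cases in which the ACD is tried first, the one that clears stays in the ACD-only group. The one that does not clear, and then receives thrusts or back blows, moves to the multiple group. The ACD-only group keeps all its successes and loses some of its failures.

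The outcome definition adds to the problem. A later intervention can both make a case a failure and place it in the multiple group, so outcome and stratifier overlap. CPR and EMS activation raise the same difficulty as candidate factors, because an association with failure may only show that failure led to them.

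This is the one planned analysis in the article that addresses how much of the relief belongs to the ACD. The Discussion intends the results to show whether ACDs have the potential to be effective and safe, so a group that sheds failures bears directly on that reading.

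**Working it through.** The article states no sample size, expected relief rate or frequency of ACD-first use, so there is no figure to reproduce. Every input below is an assumption.

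**Inputs.** r = true relief by the ACD when it is used first. q = share of ACD-first failures that then receive another technique. f = share of all cases in which the ACD is used first. s = success of a later technique after a failed ACD.

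**Step 1: the ACD-only group.** All successes (r) stay, and failures stay only if nothing else is tried, (1−r)(1−q):

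observed relief = r / [r + (1−r)(1−q)]

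For r = 0.60:
- q = 0: 0.60/(0.60+0.40) = 60%
- q = 0.5: 0.60/(0.60+0.20) = 75%
- q = 0.7: 0.60/(0.60+0.12) = 83%
- q = 0.9: 0.60/(0.60+0.04) = 94%

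The same formula over a wider range:

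| True relief r | q = 0 | q = 0.5 | q = 0.7 | q = 0.9 |
|---|---|---|---|---|
| 40% | 40% | 57% | 69% | 87% |
| 60% | 60% | 75% | 83% | 94% |
| 80% | 80% | 89% | 93% | 98% |

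The result reaches 100% only if q = 1.

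**Step 2: the multiple group.** Assume that the ACD works equally well in every case. This group then holds the cases with a technique before the ACD (1−f) and the ACD-first failures that went on to something else, f(1−r)q.

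- *Relief credited to the ACD attempt:* (1−f)r / [(1−f) + f(1−r)q]. With r = 0.70 and f = 0.50, q = 0.5 gives 0.35/0.575 = 61%, and q = 0.9 gives 0.35/0.635 = 55%. The ACD-only group shows 82% (0.70/0.85) and 96% (0.70/0.73).
- *Relief meaning clearance by any means:* [(1−f)r + f(1−r)qs] / [(1−f) + f(1−r)q]. With r = s = 0.70 this is 70% for any f and q. With r = 0.50, s = 0.70, f = 0.50 and q = 0.9 it is 0.4075/0.725 = 56%, above the true ACD rate. The ACD-only group is inflated as in step 1 under this reading too.

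**Step 3: what a test would show.** The article does not say outright that the two strata will be tested against each other. If they are, a simulation with no true difference (r = 0.70, f = 0.50, relief credited to the ACD, 4000 replicates, chi-squared test or Fisher's exact test for small expected counts) gives these rates of p < 0.05:

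| N (assumed) | q = 0 | q = 0.5 | q = 0.9 |
|---|---|---|---|
| 50 | 4.5% | 35% | 93% |
| 100 | 5% | 67% | >99% |
| 200 | 5% | 92% | 100% |

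With strata defined only by what preceded the first ACD attempt, the rate is 4.3–5.4% in all nine settings.

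**Step 4: EMS activation as a factor.** Let a be the share of cases in which EMS is called before, or regardless of, the ACD result. In the rest, assume a call follows 90% of failures and 20% of successes, with r = 0.70. For a = 0.5, EMS is called in 0.5+0.5×0.2 = 60% of successes and 0.5+0.5×0.9 = 95% of failures. Relief with EMS is 0.42/(0.42+0.285) = 60%, and without EMS 0.28/(0.28+0.015) = 95%. For a = 0.2 and a = 0.8, relief with EMS is 48% and 67%, still against 95% without. If the call does not depend on the ACD result, both groups show 70%.

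**The case against.** The strongest reply is that the plan's own example of multiple interventions puts back blows before the ACD, and the Introduction describes ACDs as marketed for use after traditional techniques fail. Such cases are classified before the ACD result is known. This stands, and it limits how far stratum membership depends on failure. It does not remove the bias, because the ACD-only group is filled by ACD-first cases, and the example does not keep those of them that later received another technique in that group.

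The Discussion also disclaims any percentage effectiveness. That limits the harm, but the reason given is self-report sampling, not this mechanism. Proportions with confidence intervals and association tests are still planned.

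Each outcome is assigned by a medical researcher and checked by a physician. That guards against careless coding, but it cannot settle a rule that does not say whether relief refers to the ACD attempt or to the episode. A condensed article may leave detail to a fuller document, but here the rule and its rationale are both stated.

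CPR and EMS are not named as tested factors. This follows only from reading the test sentence with Table 1 and Aim One. EMS activation is also not the same as EMS intervention being required, and a call may precede ACD use.

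The stratification was meant as a caution against crediting one technique with relief. The caution is sound. Attributing relief to synergy goes further than the design allows, since an ineffective technique followed by an effective one leaves the same record.

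**Conclusion.** The point holds in a limited form. With no time anchor, ACD-only relief is biased upward whenever failed ACD-first cases receive another technique. At an assumed true relief of 60%, the observed figure runs from 60% (no failures receive another technique) to 94% (90% do). The size rests wholly on assumed inputs, but the direction does not.

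A reader might infer more than the article supports:

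- *That ACD-only use succeeds by construction, or that the strata are determined by ACD failure.* Failures with no further attempt stay in the ACD-only group, and cases with an earlier technique are in the multiple group whatever the ACD does.
- *That combined use must look worse.* This depends on the share of ACD-first cases and on whether relief refers to the ACD attempt or the episode.
- *That CPR and EMS must be associated with failure whatever the device does.* This needs their use to depend on the ACD result.
- *That hospital removal, or CPR after clearance, will be miscoded.* The article does not show this. A patient who needs hospital removal may not meet the symptom-resolution part of the definition.

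**What to change.** 1. Stratify by what was done before the first ACD application: ACD first, versus ACD after at least one other technique. State that the second group selects refractory obstructions, so the contrast is descriptive and does not isolate the device.
2. Code relief against the ACD attempt. Count a case cleared only by a later technique as not relieved by the ACD, and report final clearance by any means as a separate outcome.
3. Report techniques used after the ACD, CPR and EMS involvement descriptively, as consequences. Do not test them as factors for relief unless they are known to have preceded the ACD.
4. Replace the synergy explanation with a statement that relief after several techniques cannot be attributed to any one of them.

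The cost is protocol wording and recoding of the intervention data. The survey itself is not shown. If it does not already record the order of interventions, one question is needed.
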